### Trial design

This 5-year project uses a 2-stage parallel group, two-arm, superiority randomized controlled trial (RCT) design with a 1:1 allocation ratio to evaluate a brief, practical adherence intervention called Individualized Texting for Adherence Building – Cardiovascular (iTAB-CV), delivered via interactive text messaging, along with self-monitoring (SM) compared to SM alone. The underlying premise is that improving adherence to antihypertensives in BD is likely to be an efficient path to improving health outcomes in a vulnerable population. The intervention is suitable for primary care or mental health settings and has potential for broad scale-up. Findings on the relationship between habit strength, medication attitudes, mood, and adherence in this project will be generalizable to other populations.

In considering the appropriate comparator to iTAB-CV in this efficacy trial, based on Mohr et al.’s seminal paper on the selection of a control condition for RCTs [37], SM will be composed of monitoring pills, blood pressure (BP), and mood as it is generalizable to standard clinical care. Each of these elements has been shown to have some efficacy in lowering SBP [38] and would allow us to determine whether iTAB-CV is efficacious above and beyond improvement yielded from implemented current clinical recommendations. The SM process for all participants involves instructing them to monitor their medication taking using an automated pill-monitoring device, take their BP weekly with a home BP monitor, and rate their mood weekly in response to a text reminder.

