As seen in Fig. 1, the entire observation duration will be 12 months. In stage 1, after consenting and passing screen, participants will receive and be trained on the use of an automated pill-monitoring device called eCAP™ (manufactured by Information Mediary Corporation, Ottawa, ON, Canada) to track use of their antihypertensive medication. Participants will use the eCAP™ for 2 months until coming in for their baseline assessment. At that time, they will be randomized on a 1:1 basis to participate in either iTAB-CV + SM or SM alone. Both interventions will be provided for 2 months with an interim phone assessment for adherence. At the end of this 2 month stage, participants will come in for an in-person assessment.

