### Sample size calculations

Power analyses are based on computations from the Repeated Measures and Sample Size (RMASS) [72] with inputs estimated from prior study data. Our projected sample size is *n* = 200, with 100 participants per arm. In this power analysis, the research team will assume type I error levels of 0.025 for each of the two primary analyses, using Bonferroni correction to account for multiple comparisons. Conservatively, for this study, the researchers will assume 25% attrition based on a previous 12 month trial conducted by members of the study team with individuals with comorbid serious mental illness and diabetes [73]. For sample size requirement for aim 1, the investigators used past-month TRQ as an approximation of expected and longer-term maintenance adherence status and considered primary outcomes to be at 3 months. The investigators expect similar or even greater effect sizes at 4 months given the longer treatment duration. In the pilot study, there was 23.10% improvement in TRQ observed for iTAB-CV. The control comparator for the efficacy trial will be SM of adherence, BP, and mood. Based on the literature, no improvement in self-reported adherence was reported in a similar control arm [74]. The study staff thus assume no change in adherence. In a BD adherence RCT, 7% improvement was observed in the control arm. Hence, the investigators conservatively project a 7% mean improvement in adherence among controls. Thus, (1) there is a mean difference of 16.1% in adherence after 4 months between arms and (2) suppose autoregressive (AR(1)) model covariance structure with correlation coefficient of 0.44 and an error variance of 308, as estimated value from the data. With assumed attrition of 25%, for a 2-sided test of the treatment by time interaction effect being equal to zero, and with alpha = 0.025 and power = 0.80, the required total sample size is approximately 78.

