From the pilot data, mean screen SBP was 144.81 (SD 15.46). Change from screen to 3 months with the iTAB-CV intervention saw a mean reduction in SBP of 8.78. Reductions in BP of at least 2 mmHg can significantly reduce the incidence of cardiovascular disease and its complications in both hypertensive and normotensive individuals, and reductions of the magnitude seen in this team’s pilot work is well above thresholds that are considered clinically meaningful [75]. Based on our preliminary mixed model, the researchers also observed compound symmetry correlation parameter value of 0.36. This covariance model had similar model fit as with an AR(1) model in terms of AIC/BIC criteria and parameter estimate values. The researchers will assume no SBP pressure change is observed in the SM arm and estimated error standard deviation of 15.46, as observed [38]. Finally, in a linear mixed model with participant-level random effects, with two-sided type I error of 0.025, power = 0.80 for the projected sample size of 182 participants. The study staff will target a sample of 200 for the study to allow for some deviation from assumptions. Thus, the researchers should have sufficient statistical power for the first 2 primary aims.

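### The 80% power for SBP sets the pilot's whole fall from screening against zero change under self-monitoring, which conflicts with the protocol's account of its comparator and with its run-in design

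*Protocol article*

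**What the plan says.** All references are to the Protocol article.

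- *Sample size calculations* takes the SBP effect from the pilot: "Change from screen to 3 months with the iTAB-CV intervention saw a mean reduction in SBP of 8.78". For the comparator it states "The researchers will assume no SBP pressure change is observed in the SM arm". It then reports "with two-sided type I error of 0.025, power = 0.80 for the projected sample size of 182 participants", raises the target to 200 as a margin for departures from the assumptions, and concludes that power is adequate for both primary aims.
- *Trial design* describes the self-monitoring (SM) comparator of pills, blood pressure and mood differently: "Each of these elements has been shown to have some efficacy in lowering SBP [38". It says the trial is to show benefit beyond that.
- *Participants* requires an average SBP of at least 130 mmHg at screening. *Equipment and devices* issues the BP monitor at screening and sets an 8-week monitored phase before the intervention. Randomization follows at the month 2 baseline, after a video shown to everyone.
- *Data analysis plan* makes treatment by time, to month 4 (V2), the primary inference for SBP.
- For adherence, *Sample size calculations* subtracts a 7-point control improvement from the pilot's 23.10 points. Nothing is subtracted for SBP.

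**The concern.** The quantity being powered is a between-arm difference in change after randomization. The quantity put into the calculation is a within-group change in treated pilot participants, starting at screening. The two are equal only if nothing lowers SBP between screening and baseline and nothing lowers it afterwards in the SM arm.

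The protocol gives reasons to doubt both conditions. It says SM has some efficacy on SBP. It enrols on a high screening value, so some regression to the mean is to be expected. It lengthened the run-in because pilot adherence rose between screening and baseline. Any such fall comes before the tested contrast or appears in both arms.

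SBP is the outcome that fixes the sample size (182, against about 78 for adherence). If the net difference is smaller than 8.78 mmHg, readers will hold a non-significant result against a claim of 80% power that rested on a larger effect than the design isolates.

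**Working it through.** **Inputs from *Sample size calculations*:** difference 8.78 − 0 = 8.78 mmHg; SD 15.46; compound symmetry (CS) correlation 0.36; two-sided alpha 0.025; power 0.80; attrition 25%; 1:1 allocation.

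**Assumed, because not stated:** three visits (baseline, V1, V2), and attrition building linearly to 25% by V2 (retention 1, 0.875, 0.75).

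**Step 1. Variance.** The test is treatment by linear time in a mixed model. With V = SD² × R, each dropout pattern k (share p_k, visits 1 to k) contributes p_k X_k′V_k⁻¹X_k to the information. The variance of baseline-to-V2 change per participant is v = 2² × [information⁻¹] for the slope.

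- No attrition: v = 2 × 15.46² × (1 − 0.36) = 305.9
- 10% attrition by V2: v = 327.9
- 25% attrition by V2: v = 370.1
- 25% attrition, AR(1) with 0.36 per visit: v = 486.5

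**Step 2. Reproduce the plan's figure.** N = 4(z₀.₉₈₇₅ + z₀.₈₀)² v / δ² = 4 × (2.241 + 0.842)² × 370.1 / 8.78² = 182.5, against the stated 182. Nearby set-ups give similar values: 185.1 with two time points, and 181.1 with four equally spaced visits and division by 0.75. So 182 is consistent with the full 8.78 mmHg being used as the between-arm difference.

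**Step 3. Detectable difference at N=200.** SE = √(4 × 370.1 / 200) = 2.721. The detectable difference is 3.083 × 2.721 = 8.39 mmHg, so the margin from 182 to 200 absorbs 8.78 − 8.39 = 0.39 mmHg. With 10% attrition the detectable difference is 7.90 mmHg (margin 0.88). With none it is 7.63 mmHg (margin 1.15).

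**Step 4. Power at N=200** if part of the 8.78 is shared by the SM arm or occurs before baseline. Power = Φ(δ/SE − 2.241). The 0 to 4 mmHg range is an assumption, since the documents give no size.

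| Shared or lost (mmHg) | Net δ | CS, 25% attrition | CS, 10% | CS, 0% | AR(1), 25% | N for 80% (CS, 25%) |
|---|---|---|---|---|---|---|
| 0 | 8.78 | 0.84 | 0.88 | 0.90 | 0.72 | 183 |
| 1 | 7.78 | 0.73 | 0.79 | 0.82 | 0.60 | 233 |
| 2 | 6.78 | 0.60 | 0.66 | 0.69 | 0.47 | 307 |
| 3 | 5.78 | 0.45 | 0.51 | 0.54 | 0.35 | 422 |
| 4 | 4.78 | 0.31 | 0.35 | 0.38 | 0.24 | 616 |

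As one illustration, applying the protocol's own control share for adherence gives 8.78 × 7/23.1 = 2.66 mmHg, a net 6.12 mmHg and power 0.50 (CS, 25% attrition).

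The AR(1) column is a sensitivity case. It is relevant because the protocol says "This covariance model had similar model fit as with an AR(1) model in terms of AIC/BIC criteria and parameter estimate values", but the pilot's visit spacing is not given, so 0.36 per trial visit is assumed.

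**The case against.** **Some efficacy for SM has no size or time scale.** Monitors and pill caps are in use for 8 weeks before randomization, so the reaction to monitoring may have settled by baseline. Little further SM change could then coexist with *Trial design*. This is fair, but it does not help an 8.78 mmHg counted from screening: a fall that settles before baseline is then lost from the treated arm's change too.

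**The shared citation.** A reader might infer that reference 38 is cited for two opposite claims. In *Sample size calculations* it follows the SD, so what it supports there is unclear, and the source is not at hand. The conflict lies in the two statements, not in the reference.

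**Is the power shown not to be delivered?** A reader might infer that the trial cannot detect a realistic difference. The documents do not support that. They size no SM fall, pre-baseline SBP fall or regression to the mean. The pilot's pre-baseline improvement is reported for adherence only, and the pilot's entry criteria are not given.

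**Attrition and model.** The 25% comes from a 12-month trial and is applied here in full by V2. *Missing data* reports 0% in the pilot and 20% in earlier studies. A baseline-adjusted analysis, which *Data analysis plan* lists as an alternative, would also do better. A two-point version (SE = √(4 × 15.46² × (1 − 0.36²)/150) = 2.355) gives 0.93, 0.86 and 0.74 for 0, 1 and 2 mmHg lost, with a detectable difference of 7.3 mmHg. This stands as a qualification: the margin is roughly 0.4 to 1.5 mmHg, depending on model and attrition. At 2 mmHg lost, power is below 0.80 in every case shown in the table and in this version; baseline adjustment with 10% attrition gives 0.82.

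**Treatment duration.** The remark "The investigators expect similar or even greater effect sizes at 4 months given the longer treatment duration" may look like further support for an inflated SBP effect, since "Both interventions will be provided for 2 months with an interim phone assessment for adherence" and month 4 counts from screening. But it belongs to the adherence calculation and is not used for SBP, and the pilot's exposure by its month 3 is not stated. It forms no part of this point.

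**Conclusion.** The point holds as a defect in the stated basis for SBP power. The arithmetic behind 182 is sound. The input is not justified: it equates an uncontrolled fall from screening with a randomized difference from a later baseline, and it assumes an inert comparator that the protocol elsewhere calls active. That the pilot was uncontrolled is inferred from the absence of any described comparator.

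Under the stated inputs, with three visits and 25% attrition by V2 assumed, power at N=200 falls below 80% once about 0.4 mmHg is shared or lost before baseline, and it runs from 0.84 down to 0.31 across 0 to 4 mmHg. With 0 to 10% attrition the tolerance is about 0.9 to 1.2 mmHg. How much is actually shared is unknown, so the claim of adequate power is unsupported, not disproved. The adherence calculation is unaffected. This should be fixed, but no test, error rate or analysis has to change.

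**What to change.** In *Sample size calculations*:

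1. Reconcile the zero-change assumption for the SM arm with *Trial design*, either by stating a non-zero SM fall or by explaining why none is expected after the run-in.
2. Base the SBP effect on net change from the randomization baseline, recomputing the pilot change from pilot baseline instead of screening.
3. Replace the single 80% figure and the closing assurance of adequate power, as they concern SBP, with the detectable difference at N=200 (about 8.4 mmHg under the stated inputs, 7.6 to 7.9 mmHg with 0 to 10% attrition). Add a power table for SM-arm falls of 0 to 4 mmHg.
4. State the visits, the timing of attrition and the covariance structure behind the table, with AR(1) as a sensitivity case.

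The cost is rewording, one reanalysis of pilot data already held, and a less favourable power statement. No extra enrolment is needed.

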### Missing data

Preliminary analyses will determine factors that are associated with attrition effects. Attrition rates in the pilot iTAB-CV adherence study was 0%. In the team’s previous BD adherence studies, attrition rates were 20%. Data that remain missing despite retention efforts will be accommodated in our analyses and their impact evaluated through sensitivity analyses. The research team will study reasons for dropout and identify covariates associated with dropout by 4 months through binary regression, including the treatment variable. Differential attrition by key covariates such as age, sex, and BD diagnosis will also be examined such as through log rank tests. These models can be estimated without bias under the missing at random (MAR) assumption [76] and provide valid analysis when the covariates associated with missingness (if any) are included in the mixed model. Researchers will conduct assessment of the MAR assumption by pattern mixture models that relax the MAR assumption, while analyzing the sensitivity of treatment by time interaction effects. Researchers will also consider selection models to assess sensitivity of findings to the MAR assumption in a Bayesian Markov Chain Monte Carlo framework [77, 78].

### Data and safety monitoring board (DSMB)

As participants in the study are a vulnerable population, we recognize the need for a careful data and safety monitoring plan to ensure the well-being of the participants in this study and the scientific integrity of the project. The investigators will use an existing DSMB in the Department of Psychiatry at Case Western Reserve University (CWRU) chaired by a psychiatrist who is independent from the investigators. Other members of the DSMB include a doctoral level statistician, a data analyst, and an experienced member of the department research staff. All members will be independent from the sponsor and competing interests.

The Chair of the DSMB will conduct real-time monitoring of all serious adverse events (SAE) that occur. SAEs are defined as events that result in any of the following: death, a life threatening experience, inpatient hospitalization or prolongation of existing hospitalization, a persistent or significant disability/incapacity, or a congenital anomaly/birth defect (or an event that may require medical or surgical intervention to prevent one of the outcomes listed above). The relationship of the SAE to study participation will be determined by the PIs. This assessment will occur within 24 h of notification of the SAE. For those situations where the SAE is determined to be study related, the DSMB Chair will review the SAE within 24 h and determine whether it is expected or unexpected. The DSMB Chair will ensure that the SAE is reported to the IRB according to established IRB guidelines. The DSMB meets at least semi-annually to review all adverse events.

The PIs will hold weekly meetings with study staff to review study progress and any issues that may come up regarding adverse events. A summary report of all adverse events will be submitted to the National Heart, Lung, and Blood Institute annually and at the end of the study. Adverse events will be identified by the study investigators and/or qualified research assistants. All adverse events, whether considered serious or not, will be recorded and reviewed by the study PIs on an ongoing basis, and reported to the IRB according to local IRB policy.

Given that this is deemed a minimal risk trial, there will be no interim analyses or stopping guidelines. There will be no post-trial care or compensation for those who suffer harm from trial participation. All participants will continue with their providers during and following the trial. Any participant at risk for imminent harm to self or others will be handled on a case by case basis. Participants will be terminated from the trial if deemed unsafe to continue in study procedures by the PI or the participant’s clinician (such as for worsening condition or increased harm risk), if the participant requests to be removed or withdraws consent, or if the participant is lost to follow-up. Since the intervention is an addition to their regular treatment and does not include medication, there will be no follow-up with research team.

### Data dissemination

Following completion of the last trial participant, results regarding the primary outcomes of the trial will be submitted for publication within 1 year of the final study visit. All final peer-reviewed manuscripts that arise from this proposal will be submitted to the digital archive PubMed Central. The data generated in this grant will be presented at national or international conferences and published in a timely fashion in journals in the field of primary care, HTN, psychiatry, behavioral medicine, BD, adherence, and behavioral trials, among others. This will ensure that the appropriate audience has access to the findings of the trial. Similarly, data from the trial will be presented at conferences focused on primary care, behavioral medicine, and psychiatry.

## Discussion

This project is innovative in that it focuses on common chronic health conditions in a high-risk group of individuals, those with poorly controlled HTN and comorbid mental illness. This innovation uses a technology-facilitated novel health promotion approach with promising pilot data and a theoretical model which views sustained medication-taking behavior in the context of habit formation. The study represents a first-ever adherence-based RCT specifically targeting BP and mental health symptom control in people with BD and includes implementation elements in the study design in order to inform future scale-up.

Individuals with BD tend to have erratic lifestyles, and the present intervention is not dependent on frequent contact between provider and patient. Rates of medical clinic attendance for people with BD are often poor and iTAB-CV addresses this problem by administering the intervention on a mobile phone [79]. Persons of lower socioeconomic status often use a mobile phone over a landline phone because of frequent address changes and adults living in poverty represent a greater proportion of cellphone-only households [80]. In the pilot data with the target population, 73.7% were African Americans, 73.7% were on Medicaid, and 87% of the sample had a cellphone. The majority of effort in this texting intervention is in the initial programming of the automated system. Once the script is in place, the intervention can be extended for longer periods of time, modified to increase the pool of queries and reminders, and altered to include additional medications.

Because the intervention asks the participant to respond to reminders and queries, the intervention is interactive unlike an alarm clock or other programmed devices. Previous studies show that the interactive properties of texting were often so well accepted that some participants elected to receive texts after the study ended [50]. iTAB-CV is flexible and can send reminders consistent with the participant’s schedule. If medications are switched during the study, iTAB-CV can be updated. The iTAB-CV intervention is highly scalable within and across patient populations.

In summary, this proposal addresses an important but understudied area: how to improve BP control in people with BD. A novel intervention that uses a model of habit formation, remediates for prospective cognitive or planning deficits, is customized, addresses both psychotropic and non-psychotropic non-adherence, and is delivered via mobile phone has the potential to improve physical and emotional health. Promising preliminary data on iTAB-CV suggests that it is feasible, highly acceptable and effective. This trial has the potential to advance care for this high-risk population and will be amenable to broad scale-up for other challenging comorbid populations.

## Trial status

We used the protocol version approved on April 21, 2021, and anticipate starting recruitment for the clinical trial in June of 2021, and completing recruitment by the end of 2024.

## Data Availability

The authors of this paper at CWRU will have full access to the final trial dataset. Authors at UCSD will have access to de-identified data. The de-identified dataset analyzed for the current study and statistical code are available from the corresponding author on reasonable request, as is the full protocol.

## Abbreviations

iTAB-CV: Individualized Texting for Adherence Building – Cardiovascular
RCT: Randomized controlled trial
CV: Cardiovascular
BD: Bipolar disorder
SBP: Systolic blood pressure
HTN: Hypertension
SPRINT: Systolic Blood Pressure Intervention Trial
AHA: American Heart Association
SM: Self-monitoring
BP: Blood pressure
IRB: Institutional Review Board
SAB: Stakeholders Advisory Board
REDCap: Research Electronic Data Capture
BHS: British Hypertension Society
MI: Mobile interventionist
RA: Research assistant
TRQ: Tablets Routine Questionnaire
BPRS: Brief Psychiatric Rating Scale
MADRS: Montgomery-Asberg Depression Rating Scale
MASES-R: Medication Adherence Self-Efficacy Scale
SRHI: Self-Report Habit Index
BMQ: Beliefs about Medicines Questionnaire
AMSQ: Attitudes toward Mood Stabilizers Questionnaire
MINI: Mini-International Neuropsychiatric Interview
CCI: Charlson Comorbidity Index
REALM-R: Rapid Estimate of Adult Literacy in Medicine Revised
RMASS: Repeated Measures and Sample Size
AR(1): Autoregressive
CWRU: Case Western Reserve University
MAR: Missing at random
DSMB: Data Safety and Monitoring Board
SAE: Serious adverse events
